## Sample Size Calculation and Outcome Variable(s)

For each survey round (weeks 1 to10, 12 to 21 , 23 to 32 weeks) we are determining estimates of zinc, ORS and antibiotic use (prevalence). With each new interval we will be sampling from the same sites, but will carry out a new random selection of clusters in which cases will be identified.

As depicted in figure 1, for each survey round the number of subjects by site and location is as follows:

Location Sites N/site N/location

City corporations Slums x 2 320 640

Non-slums x 2 320 640

Urban Municipalities x 3 320 960

Rural Upazillas x 3 320 960

Based upon WHO EPI cluster survey methods, the design effect is estimated to be 2.0 (11)

a. Prevalence of zinc treatment by site: Setting confidence at 0.95 and a minimal detectable error of a 5% for a prevalence estimate within a site, assuming the baseline overall prevalence of zinc coverage to be 10%:

(Z alpha )2 (P)(1-P)

N/site = x 2 (cluster adjustment design effect)

d 2

N/site = 276 cases

b. Trends in use of ORS and antibiotics by site: Setting confidence at 0.95 and a minimal detectable error of 10% around a prevalence of 50% of cases being treated with ORS or an antibiotic;

N/site = 198

d. Comparison of two proportions (hypothesis testing):

To examine whether zinc coverage in urban or rural locations is significantly different among males vs females, setting the level of conficence at .95 (one-sided), power at .80, minimal detectable difference 10%, assuming an overall prevalence of 25% coverage by the third cycle

(Z alpha + Z beta)2 (P)(P-1) x 2

N/gender/location = x 2 (cluster adjustment design effect)

d 2

N/location = 461

Given these estimates, we will have the power to detect smaller differences in the rural and municipality

locations. In the City Corporations sites the power is adequate if we combine slum and non-slum populations. Keeping them separate will allow for a minimal detectable difference of 12%.

Measurement: An interviewer completed questionnaire essentially the same as the baseline questionnaire (questions on expenditures have been modivied to provide greater clarity on commodity purchases vs. service cahrges). . The questionniare requires about 30 minutes to complete. Questions cover host, illness and socio-demographic characteristics followed by household diarrhea management practices and expenditures on the identified case. Socioeconomic status will be estimated by determination of a household asset score based upon ownership of consumer items, dwelling characteristics, toilet facilities used, and other household characteristics that are related to wealth status (12). Each asset is assigned a weight generated through principal components analysis and then standardized scores assigned (13). For any household all asset scores will be summed and then sub-grouped into quartiles.

Sixteen FRAs will be trained to carry out case finding and household interviews. They will be supervised by two FROs. The entire data collection team will be supported by an NOA level co-investigator who has had experience with the baseline surveys.

## Facilities Available

Describe the availability of physical facilities at the place where the study will be carried out. For clinical and laboratory-based studies, indicate the provision of hospital and other types of patient’s care facilities and adequate laboratory support. Point out the laboratory facilities and major equipment that will be required for the study. For field studies, describe the field area including its size, population, and means of communications.

This study will be supported by the SUZY Project management team and office facilities will be provided by the HSID division. Logistical support will be provided by the field site managers in Abhoynagar, Mirsarai, Kamalapur and Mirpur.

## Data Safety Monitoring Plan (DSMP)

All clinical investigations (biomedical and behavioural intervention research protocols) should include the Data and Safety Monitoring Plan (DSMP) to provide the overall framework for the research protocol’s data and safety monitoring. It is not necessary that the DSMP covers all possible aspects of each elements. When designing an appropriate DSMP, the following should be kept in mind.

1. All investigations require monitoring;
2. The benefits of the investigation should outweigh the risks;
3. The monitoring plan should commensurate with risk; and
4. Monitoring should be with the size and complexity of the investigation.

Safety monitoring is defined as any process during clinical trails that involves the review of accumulated outcome data for groups of patients to determine if any treatment procedure practised should be altered or not.

**Not applicable**

## Data Analysis

Describe plans for data analysis. Indicate whether data will be analyzed by the investigators themselves or by other professionals. Specify what statistical software packages will be used and if the study is blinded, when the code will be opened. For clinical trials, indicate if interim data analysis will be required to monitor further progress of the study.

The investigative team will carry out the data analysis. Data entry and general management will be done by the Data Resources and Surveillance Unit of the Division. Data will be entered and analyzed using SPSS version 12.0. Absolute counts, proportions and means with 95% confidence intervals were calculated. These and the regression analyses will be completed using STATA version 9, cluster survey program , that accounts for potential within cluster homogeneity. The analyses will stratified by location of residence into rural, municipal and city corporation households. The latter are further sub-grouped as predominantly slum or non-slum populations. For differences in categorical outcomes crude relative risks and 95% confidence intervals will determined. Multiple logistic regression models were tested for the prediction of health seeking behaviours and antibiotic, ORS or zinc treatments received. Of particular interest is the identification of disparities in health provider utilization, diarrhea treatment practices and illness expenditures by gender, asset quartile (household wealth) and geographic location of the household (rural, municipal or city corporation). The hypotheses to be tested are that significant (p<.05) differences in the management of childhood diarrhea favoring males, higher asset households and urban populations would be found.

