Appendix 5: Detailed Budget

Appendix 6: Questionnaire

[Check-List](#__RefHeading___Toc132346870)

Check here if appendix is included

| Project Summary Describe in concise terms, the hypothesis, objectives, and the relevant background of the project. Also describe concisely the experimental design and research methods for achieving the objectives. This description will serve as a succinct and precise and accurate description of the proposed research is required. This summary must be understandable and interpretable when removed from the main application. **(Please keep as brief as possible).** |
| --- |
| Principal Investigator(s): [name] |
| Research Protocol Title: Monitoring the Impact of the SUZY Project role-out of Zinc as a Treatment for Childhood Diarrhea |
| Total Budget US$: 208,423 Beginning Date : 01/09/06 Ending Date: 15/06/07 |
| This is a repeat, ecologic survey to document changes in zinc coverage for childhood diarrhea, coinciding with the national roll-out of “Baby Zinc”. The surveys have been stratified by location; rural, urban municipalities, and city coprportation slum and non-slum populations.  In addition to zinc coverage, the surveys will monitor changes in the use of ORS or antibiotics, expenditures on diarrheal illnesses and other management practices. The surveys have been powered to identify disparities in care based upon gender, income and location of households.  The survey field sites have been purposively selected in order to facilitate comparisons with the baseline national coverage survey carried out in 2003/4. These include rural upazilla (Mirsarai, Abhoynagar, Hobiganj), urban municipalities (Khulna, Sylhet, Camila), and City Corporation zones (slum: kamalapur, Mirpur and non-slum Green--------- The same interviewer administered questionnaire will be used.  The results of this study will provide guidance for public, private and NGO delivery systems as they jointly endeavor to reach all under-five children with zinc treatment of any diarrheal disease episode. |
| KEY PERSONNEL (List names of all investigators including PI and their respective specialties)     | Name | Professional Discipline/ Specialty | Role in the Project | | --- | --- | --- | | 1. [name] | Health services research | PI | | 1. [name] | Statistician | analyses, data management | | 1. [name] | Field studies | Coordination of survey conduct | |

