## Hypothesis to be Tested:

Concisely list in order, the hypothesis to be tested and the Specific Aims of the proposed study. Provide the scientific basis of the hypothesis, critically examining the observations leading to the formulation of the hypothesis.

Over the planned 8 months of observation;

H1: That there will be a significant, upward trend in use of zinc for the treatment of childhood diarrhea.

H2: That there will be a significant downward trend in the use of antibiotics for the treatment of non-bloody childhood diarrhea

H3: That there will be disparities in zinc treatment coverage on the basis of household income status. gender oand location (rural, urban, city corporation slum and non-slum populations).

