## Research Design and Methods

Describe in detail the methods and procedures that will be used to accomplish the objectives and specific aims of the project. Discuss the alternative methods that are available and justify the use of the method proposed in the study. Justify the scientific validity of the methodological approach (biomedical, social, or environmental) as an investigation tool to achieve the specific aims. Discuss the limitations and difficulties of the proposed procedures and sufficiently justify the use of them. Discuss the ethical issues related to biomedical and social research for employing special procedures, such as invasive procedures in sick children, use of isotopes or any other hazardous materials, or social questionnaires relating to individual privacy. Point out safety procedures to be observed for protection of individuals during any situations or materials that may be injurious to human health. The methodology section should be sufficiently descriptive to allow the reviewers to make valid and unambiguous assessment of the project.

Study design: A repeat, ecologic survey in three rural upazillas, three municipalities and two city coprporation slum plus two non-slum zones is proposed. The survey team will complete three survey cycles per site, each cycle estimated to require 10 weeks to complete. The surveys will be carried out from September, 2006 through April, 2007 (SUZY Project funding ends in June, 2007).

Survey Populations

a. Rural: The sub-districts of Mirsarai, Abhoynagar and Hobiganj have been purposively selected. Within

each sub-district we will randomly select 20 clusters based upon a listing of all wards in the subdistrict.

All wards will be enumerated and then randomly selected.

b. Urban: The district municipalities of Khulna, Camila and Sylhet have been purposively selected. Twenty

clusters will be randomly selected within each municipality. Clusters are defined as geographic units

(“strata”) within the municipality that will be enumerated.

c. Dhaka City Corporation: slum zones of Kamalapur and Mirpur, non-slum zones (and wards) of Green

Road and Old Dhaka. Within each zone 20 clusters will be selected. Clusters are geographically defined

population“units” based upon the most recent census

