***No potential risks have been identified.***

1. If study involves an interview, describe where and in what context the interview will take place. State approximate length of time required for the interview.

***The interview will take place in the child’s home at a time convenient for the parent/guardian. It requires approximately 20 minutes to complete.***

1. Assess the potential benefits to be gained by the individual subject as well as the benefits which may accrue to society in general as a result of the planned work. Indicate how the benefits outweigh the risks.

***Following the interview, all unaware participants will be informed of the usefulness of zinc. From a societal standpoint, the findings of this survey guide the equitable scale up of zinc across Bangladesh.***

1. State if the activity requires the use of records (hospital, medical, birth, death or other), organs, tissues, body fluids, the fetus or the abortus.

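### The location part of H3 is worded for rural, municipal, slum and non-slum populations, but its planned error supports only a comparison of the ten named sites

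*Protocol*

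**What the plan says.** - **Hypothesis.** Protocol, Hypothesis to be Tested, H3 expects "disparities in zinc treatment coverage on the basis of household income status. gender oand location", where location means "location (rural, urban, city corporation slum and non-slum populations". Data Analysis repeats this as a test at p<.05 and expects the difference to favour urban populations.
- **Sites.** Research Design and Methods: "A repeat, ecologic survey in three rural upazillas, three municipalities and two city coprporation slum plus two non-slum zones is proposed". The Project Summary gives the selection rule: "The survey field sites have been purposively selected in order to facilitate comparisons with the baseline national coverage survey carried out in 2003/4". Survey Populations repeats it by type, for example: "The district municipalities of Khulna, Camila and Sylhet have been purposively selected".
- **What is random.** Only the 20 clusters inside each site are drawn at random. They are redrawn in each round, while the sites stay the same (Research Design and Methods; Sample Size Calculation).
- **Error term.** Data Analysis names a "cluster survey program , that accounts for potential within cluster homogeneity". Clusters are wards or geographic units inside a site. The Sample Size section uses a design effect of 2.0 for them. Neither section mentions variation between sites.
- **Use of the result.** The Appendix 4 abstract summary says that "the findings of this survey guide the equitable scale up of zinc across Bangladesh". No section limits the location conclusion to the ten sites.

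**The concern.** Location type varies only between sites: every child in a given site has the same location type. A rural against municipal contrast therefore carries the whole of any difference between the three upazillas and the three municipalities, whatever its cause. The planned standard error reflects only the sampling of clusters inside sites. It answers whether the average over the named rural sites differs from the average over the named municipal sites. H3 asks about populations of a type, which is a wider question.

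If sites of one type differ among themselves, the planned test will too often find a location disparity where the types do not differ, and its intervals will be too narrow for the wider question. Further rounds do not cure this, because the sites are reused and a stable site effect does not average out. The protocol intends the equity findings to inform pro-poor policy and programming, so the reach of the location claim matters.

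This is not a detail left to an SAP. The protocol itself fixes the hypothesis, the significance level and the variance method.

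**Working it through.** **1. The plan's own figures.** These come from the Sample Size section.
- Precision by site: 1.96² × 0.10 × 0.90 / 0.05² × 2 = 276.6 (plan: 276).
- Gender contrast, one-sided 5%, power 80%: (1.645 + 0.842)² × 0.25 × 0.75 × 2 / 0.10² × 2 ≈ 464 (plan: 461).
- Detectable gender difference with 320 per gender: 12.0 points (plan: 12%).

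The figures reproduce. They cover precision within a site and a gender contrast within a location. The plan has no calculation for one location against another.

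**2. Inputs for the location contrast.** From the protocol: coverage P = 0.25 (the third-cycle assumption) or 0.10 (baseline), 320 cases per site (20 clusters × 16), design effect 2.0, and k = 3 or 2 sites per type. The design effect implies a within-site cluster correlation of (2 − 1)/(16 − 1) = 1/15. Assumed, because the documents do not give it: the between-site SD, τ. The true difference between location types is set to zero.

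**3. Formulas.**
- Planned variance: SE_w² = P(1−P) × 2/320 × (1/k + 1/k)
- Variance including sites: SE_t² = SE_w² + τ² × (1/k + 1/k)
- Two-sided rejection rate: 2 × [1 − Φ(1.96 × SE_w/SE_t)]

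For 3 vs 3 sites at P = 0.25, SE_w = √(0.25 × 0.75 × 2/320 × 2/3) = 2.80 points. The factor 2/k cancels in the ratio, so 2 vs 2 sites give the same rejection rate.

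| Assumed τ (points) | SE with sites, 3 vs 3, P = 25% | Rejection, P = 25% | Rejection, P = 10% |
|---|---|---|---|
| 0 | 2.80 | 5% | 5% |
| 2 | 3.24 | 9% | 13% |
| 3 | 3.72 | 14% | 22% |
| 5 | 4.95 | 27% | 40% |
| 8 | 7.10 | 44% | 58% |

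At P = 25% the rate reaches 10% at τ of about 2.2 points. With three rounds pooled and stable site effects, it is 28% at τ = 3 and 47% at τ = 5.

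**4. Simulation check.** Beta-binomial clusters, 20 × 16 per site, correlation 1/15, 8,000 runs. At P = 25% and τ = 5 the cluster-based test rejects in 26–27% of runs with site as stratum, and in about 25% with location as stratum. At τ = 0 it rejects in about 5%.

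**5. Interval width.** For 3 vs 3 at τ = 5, the planned half-width is 1.96 × 2.80 = 5.5 points. With site variation it is 1.96 × 4.95 = 9.7 points, or about 14 points with the t value for 4 df (2.78).

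**6. What a site-level test would give.** Taking sites as the units restores the level (4.5–5.6% in simulation), on 4 df for 3 vs 3 and 2 df for 2 vs 2. At P = 25% and τ of 3 to 5 points, the difference detectable with 80% power is about 14–19 points for 3 vs 3 and 26–34 points for 2 vs 2. The latter exceeds the assumed 25% coverage itself.

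**The case against.** The strongest reply is that the planned error suits the design. Clusters are the only units drawn at random, and the sites were fixed on purpose so that results could be compared with the baseline survey. For those fixed sites a cluster-based standard error is the correct design-based one. This stands. A reader might infer that the variance method is wrong or that the test is invalid; the documents do not support that. The mismatch lies between a valid comparison of named-site averages and a hypothesis worded for populations.

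Further points:
- **Size.** No between-site SD is given, and at an SD of zero the test holds its 5% level. The stronger reading, that the plan will declare false location disparities, is not supported. The inflation is conditional.
- **Evidence for site effects.** It is tempting to infer unequal zinc promotion from Facilities Available: "Logistical support will be provided by the field site managers in Abhoynagar, Mirsarai, Kamalapur and Mirpur". That sentence concerns logistics for the survey, the campaign is described as a national roll-out, and Budget Justifications also lists support for Sylhet. The passage does not show that coverage differs by site.
- **Direction.** The hypothesis favours urban populations, so about half of the two-sided rejections would support it: about 13% at τ = 5, against 2.5% nominal. The relative inflation remains.
- **Adjustment.** The planned logistic models could absorb differences in composition between sites, which the calculation ignores. They would not remove other site effects.
- **Remedy by site-level test.** Such a test treats two or three purposively chosen sites as exchangeable draws from a type. It cannot make them representative, so it cannot be the basis for population claims either.

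**Conclusion.** The point holds in a limited form. As written, H3 and Data Analysis draw a p<.05 conclusion about location types from an error term that covers only the named sites, and nothing in the protocol narrows the claim. If sites of the same type differ, the nominal 5% test is too liberal for the stated hypothesis: about 9%, 14% and 27% at assumed between-site SDs of 2, 3 and 5 points with 25% coverage, and more at 10% coverage. These rates assume no true difference between types, an unadjusted comparison in one round, and the protocol's design effect of 2.0. The SDs are illustrations, not estimates.

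The null being tested is equality of location averages over the named sites. A reader might take it to be equality of every site, which is not what the contrast tests. Nor does the problem extend to the rest of the plan: gender and wealth contrasts made within a location, and the trends in H1 and H2 at the same sites, are not affected in this way.

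**What to change.** In Data Analysis, separate the two kinds of contrast.

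1. **Gender and asset quartile.** Keep the cluster survey analysis, with site as stratum.
2. **Location.** Report coverage with an interval for each of the ten sites. State that cluster-based p-values and intervals for location compare the named sites only. Treat statements about rural, municipal, slum or non-slum populations in general as descriptive, and word H3 and the dissemination of its results to match.
3. **Optional sensitivity check.** A site-level analysis may be shown beside these results, with a note that it assumes exchangeable sites and has low power, giving the detectable differences above for 3 vs 3 and 2 vs 2 sites.

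The cost is protocol wording and one table from data already planned, with no extra interviews. The drawback is that the general location claim becomes weaker.

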## Ethical Assurance for Protection of Human Rights

Describe in the space provided the justifications for conducting this research in human subjects. If the study needs observations on sick individuals, provide sufficient reasons for using them. Indicate how subject’s rights are protected and if there is any benefit or risk to each subject of the study.

This study addresses childhood diarrhea, a major contributor to pediatric morbidity and mortality in Bangladesh. Zinc, in the doses to be prescribed in this study, is not known to cause any major, harmful health events. It may increase the likelihood of transient vomiting. Potential, minor side effects are favorably balanced by the proof of its effectiveness in reducing the length and severity of a diarrheal episode and the decreased risk of a subsequent episode. It has also been demonstrated to reduce subsequent mortality by 50%.

Parents of children with diarrhea will be interviewed once during or shortly after an episode. Any child found to be moderately to severely dehydrated or experiencing bloody diarrhea will be referred to the nearest MOHFW or NGO health facility.

This study is not prescribing treatment, but does promote its use through a mass media campaign and provider sensitization + training. It will monitor trends in treatment practice, with a focus on zinc as a treatment. All caretakers/parents interviewed will be requested a verbal consent.

## Use of Animals

Describe in the space provided the type and species of animals that will be used in the study. Justify with reasons the use of particular animal species in the experiment and the compliance of the animal ethical guidelines for conducting the proposed procedures.

Not applicable

## Dissemination and Use of Findings

Describe explicitly the plans for disseminating the accomplished results. Describe what type of publication is anticipated: working papers, internal (institutional) publication, international publications, international conferences and agencies, workshops etc. Mention if the project is linked to the Government of the People’s Republic of Bangladesh through a training programme.

The results of this study will be disseminated through peer reviewed journal publication, the Health Science Bulletin of ICDDR,B, conference presentations (national and international), workshops(national and international) and the SUZY Project technical interest group. In addition, findings will be discussed with policy makers and programmers in the public and private sectors.

